The patient is registered via a web-based system (http://www.medscinet.com/tobas) that will structure the forgoing allocation process and immediately communicate the result of the randomization (when appropriate) to the multidisciplinary team. The web-based platform is available 24 hours a day and assures concealment of the sequence until interventions are assigned. The first randomization will be stratified according to intended primary interventional management groups (surgery, radiation therapy, or embolization). A minimization algorithm will be used to ensure balance between groups with respect to: 1) presentation (hemorrhagic (Group I) versus all other presentations (Group II)); 2) according to SM AVM grade (I–II versus III–V). After the patient has been pre-randomized and placed in the appropriate arm of the study, the treatment team will verify that the intended management course is appropriate and considered optimal care for the patient. The patient will then be presented the recommendations of the multidisciplinary team (including the allocation by randomization when appropriate) and will be offered participation. There will be full disclosure of the pre-randomized nature of the study (Zelen’s design [44, 45]) to the patients, when this procedure will be used. They will then be asked to sign the consent form. Patients not willing to comply with the proposed allocation will still be offered participation in the study, but a cross-over will be recorded. Patients treated according to clinical judgment alone will be entered in the registry portion of the study (after the consent form is signed).

Justification of stratification, minimization criteria and other design choices such as Zelen’s are provided in Additional file 1.

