### Statistics

There are many components to this study (Table 2). It is important to distinguish the two randomized levels, which will be analyzed separately as randomized trials (intention-to-treat and per-protocol), and the registry portion, analyzed as an observational study.

**Table 2 Tab2:** Predefined group and subgroup analyses according to treatment allocation

Stratified randomized allocation	Groups: Intervention group versus Observation group
	Surgery subgroup versus Observation subgroup
	Radiosurgery subgroup versus Observation subgroup
	Embolization subgroup versus Observation subgroup
Randomization on pre-embolization	Groups: Embolization versus No embolization
	Embo + surgery subgroup versus Surgery alone subgroup
	Embo + radiosurgery subgroup versus Radiosurgery subgroup
Registry	
	Conservative management
	Surgical treatment (alone)
	Surgical treatment (with embolization)
	Radiotherapy (alone)
	Radiotherapy (with embolization)
	Embolization (alone)
	Embolization + surgery
	Embolization + radiotherapy
According to presentation	Unruptured AVM patients
	Ruptured AVM patients
According to SM grading	Low-grade AVM patients
	High-grade AVM patients

*AVM* arteriovenous malformation, *SM* Spetzler-Martin

Descriptive tables on demographic variables and potential risk factors will be provided to describe the groups at baseline. Continuous variables will be summarized in tables and will include the number of subjects, means, standard deviations, medians, minima and maxima. Categorical variables will be presented in tables as frequencies and percentages.

For the first RCT (interventional or conservative management strategy), the primary analysis, concerning the primary outcome (mRS > 2 or death from any cause at 10 years) of unruptured AVM patients will be analyzed using a Fisher’s exact test and the odds ratio with 95 % confidence interval will be reported. The same analysis will be performed for the ruptured group (considered a secondary analysis). All other secondary objectives and analyses for this first RCT will be analyzed in the same way.

The primary outcome of the second RCT (complete obliteration of the AVM combined with a mRS < 3; pre-surgical or pre-radiation embolization versus no embolization) will be analyzed with a logistic regression adjusted for ruptured status and intervention. Adjusted odds ratio and 95 % confidence interval will be reported. Moreover, stratified results by ruptured status and intervention will be presented.

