The patients entered in the registry will be included in secondary analyses designed to estimate treatment morbidity for each modality and natural history of untreated patients, just as an observational study, for unruptured and ruptured AVMs, for high-grade and low-grade lesions. There are four groups and eight registered subgroups (Table II). Predetermined subgroups that will be examined include: 1) according to treatment modality; 2) according to presentation (hemorrhagic versus all other presentations) and 3) according to SM AVM grade (I–II versus III–V). With a 10-year follow-up, it is likely that there will be losses to follow-up, but it is too early to estimate how many. Primary analyses will include three categories (good outcome; bad outcome; lost to follow-up). We will explore results when a best case scenario (patients lost to follow-up have a good outcome) and a worst case scenario (they have a bad outcome) are imputed.

All analyses will be done with SAS software (SAS Institute Inc., Cary, NC, USA) using a significance level of 5 %.

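### The first RCT balances allocation on modality and SM grade but tests its primary outcome with an unadjusted Fisher's exact test, forgoing about 2.5 to 6.5 points of power

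*Protocol article*

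**What the plan says.** Under Randomization and allocation of treatment options, the protocol article states: "The first randomization will be stratified according to intended primary interventional management groups (surgery, radiation therapy, or embolization". It continues: "A minimization algorithm will be used to ensure balance between groups with respect to" two factors, presentation (hemorrhagic or other) and SM grade (I–II or III–V).

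Under Statistics, the primary outcome of the first RCT in unruptured patients is tested with Fisher's "exact test and the odds ratio with 95 % confidence interval will be reported". Ruptured patients are handled apart: "The same analysis will be performed for the ruptured group (considered a secondary analysis"). Restriction to unruptured patients therefore deals with presentation. Modality and SM grade appear for this trial only as subgroups (Table 2), not in the primary test.

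The second, nested trial is treated differently: its primary outcome "will be analyzed with a logistic regression adjusted for ruptured status and intervention". All analyses use a 5 % level. The article states neither sidedness nor power.

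**The concern.** Balancing the arms on a prognostic factor removes that factor's contribution to the sampling variance of the treatment difference. An unadjusted test still counts it. The standard error is then too large, the true type I error falls below nominal, and power is given away. Fisher's exact test adds conservatism of its own because its p-values are discrete.

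This is a stated choice, not detail left to an analysis plan: the article names the primary test. Covariate adjustment was also within the authors' intentions, since the nested trial has it.

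What is at stake is efficiency. The Number of patients section says that losses over 10 years can be substantial and that an intention-to-treat analysis would need more than 540 patients. Power that can be recovered without recruiting anyone is useful here.

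**Working it through.** **Inputs.** From the article: 540 patients (270 per arm), 1:1 allocation, poor outcome 25 v 15 % at 10 years, 5 % level. Assumed: two-sided testing, and a range of odds ratios for SM grade and modality.

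**1. Reproducing the stated sample size.** With z = 1.960 and 0.8416, mean risk 0.20 and difference d = 0.10:

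n = [1.960·√(2·0.20·0.80) + 0.8416·√(0.25·0.75 + 0.15·0.85)]² / 0.10² = (1.1087 + 0.4724)² / 0.01 = 250 per arm.

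With the continuity correction, n′ = (n/4)·[1 + √(1 + 4/(n·d))]² = (250/4)·[1 + √1.16]² ≈ 270 per arm.

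This matches the stated 270. The same settings give 219 per arm for the nested trial, against 220 stated. So 80 % two-sided power with a continuity correction is the likely basis, and it suits a Fisher test. One-sided 90 % power without correction (273 and 217) is also close, so this reading is probable rather than certain.

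**2. Fisher's own conservatism, by exact enumeration at 270 per arm.**

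| Test | Size at 25 % | Power, 25 v 15 % |
|---|---|---|
| Fisher | 4.0 % | 80.6 % |
| Chi-square, unadjusted | 5.0 % | 83.3 % |

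Discreteness alone costs 83.3 − 80.6 = 2.7 points.

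**3. Adding prognostic factors.** If stratum k has risk p_k and the overall risk is p, the unadjusted variance uses p(1−p). This equals the average of p_k(1−p_k) plus the variance of the p_k between strata. With arms balanced within strata, only the first part contributes to the sampling variance of the difference. Simulation with 40,000 trials per setting and arms balanced within modality-by-grade cells gives:

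| Assumed OR, grade/modality | Size: Fisher v stratified MH | Power: Fisher v stratified MH | Gain |
|---|---|---|---|
| 1/1 | 4.0 v 5.0 % | 80.5 v 83.1 % | 2.6 |
| 2/1.5 | 3.7 v about 5 % | 81.1 v 84.6 % | 3.5 |
| 3/2 | 3.0 v about 5 % | 81.6 v 86.2 % | 4.6 |
| 5/3 | 2.2 v about 5 % | 82.9 v 89.4 % | 6.5 |

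A second layout used unequal modality shares (40, 35 and 25 %) and let the modality odds ratio span the three groups as a whole. The three prognostic settings then gave Fisher sizes of 3.8, 3.3 and 2.9 %, and power of 80.6 v 84.1, 81.1 v 85.6 and 81.1 v 87.1 %. The gain there is about 3.5 to 6 points.

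**4. Splitting the gain.** A separate run with six equal cells put the unadjusted chi-square test beside the stratified one: 83.6 v 84.3 % at 2/1.5, 84.4 v 86.4 % at 3/2, and 85.4 v 89.4 % at 5/3. Ignoring the strata therefore costs about 0.7, 2 and 4 points. The remainder is Fisher's discreteness.

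**The case against.** The strongest reply is that nothing is broken. The error is on the safe side, and the sample size appears to have been set for a Fisher-type test, which still reaches about 80 % power. This stands, and it settles the severity: what is lost is power above the apparent target.

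The second reply is that prognostic strength is assumed. This also stands. The article ties acceptable complication risk (10 to 20 %) to AVM grade and quotes permanent deficit rates of 7.1, 6.6 and 5.1 % for surgical, endovascular and radiosurgical candidates. These are treatment risks, which conservatively managed patients do not carry, and they do not yield an odds ratio for the 10-year outcome. The case with no prognostic effect must be shown beside the others. The simulations also impose balance in every cell, whereas minimisation commonly balances margins only and the primary analysis uses a subset. Fisher's true size would then lie somewhat closer to its no-prognosis value.

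Three stronger readings are tempting and unsupported:

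- A reader might infer that the trial is invalid or underpowered. It is neither on this ground.
- A reader might infer that the nested trial's test is conservative too, because its model omits SM grade. The article describes minimisation after the first randomization and does not say that it governs the second. If it does, the omission costs only about 0 to 1 power point.
- A reader might extend the point to the Table 2 subgroups. The article makes no confirmatory claim for them and concedes that each modality would eventually need 540 patients or more. Interaction tests are commonly left to an analysis plan.

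**Conclusion.** The point holds for the first RCT as a worthwhile improvement (should fix), not as a flaw that threatens validity. At the article's own sample size and rates, a stratified test gains about 2.6 points of power if modality and SM grade are not prognostic. It gains about 3.5 to 6.5 points under odds ratios from 2/1.5 to 5/3. Fisher's true size is about 4.0 % in the first case and about 3.7 to 2.2 % in the others. About 2.7 points come from Fisher's discreteness whatever the prognosis, so even a reader who doubts the assumed odds ratios has that much to gain. The results rest on two-sided 5 % testing, near-balance within modality-by-grade cells, and complete outcome data without cross-over.

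**What to change.** In Statistics, make the primary test of the first RCT a Mantel-Haenszel test stratified by intended modality (surgery, radiation therapy, embolization) and SM grade (I–II v III–V), or a logistic regression with those terms. Report the adjusted odds ratio with its 95 % confidence interval, and keep Fisher's test as a sensitivity analysis. The adjusted odds ratio is conditional on the strata and is not the same quantity as the crude one, so the proportions by arm should be shown beside it.

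Optional and minor: add SM grade to the nested trial's logistic model, and state which factors balance the second randomization.

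The cost is a change of wording. Both factors are known at allocation, no patient or visit is added, and the sample size need not change. The change should be dated and made before outcomes by arm are seen. The article reports 80 patients recruited, against a primary outcome at 10 years.

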### Medical management

Patients allocated to the medical management arm will receive no additional interventional treatment.

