### Outcomes

The primary outcome of the first RCT and of the registry is a composite of disabling stroke (resulting in modified Rankin Scale (mRS) > 2) or death from any cause at 10 years. Functional outcome status will be measured by the modified Rankin Scale, the most widely used outcome measure for stroke [43], using a standardized questionnaire administered by unblinded care personnel.

Secondary outcomes include overall mortality (all causes), overall morbidity (mRS > 2; all causes) at 1, 5 and 10 years, the occurrence of any neurological event during follow-up, the incidence of permanent (more than 3 months) disabling (mRS > 2) peri-operative (within 31 days) complications, the incidence of any peri-operative (within 31 days) complication, the incidence and number of hospital admissions, peri-treatment hospitalization lasting more than 15 days, discharge to a location other than home, occurrence of an ICH after enrollment and for up to 10 years, and occurrence of failure to eradicate the AVM (as determined by angiography) using the intended treatment modality.

The primary outcome of the nested RCT on pre-surgical or pre-radiation embolization is complete obliteration of the AVM (judged by local angiographers) combined with an independent functional outcome (mRS < 3; using a standardized questionnaire administered by unblinded care personnel) at the end of the management plan (no less than 3 months after the last procedure; no more than 3 years after radiation therapy).

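### The rule that every secondary outcome of the first RCT is analysed like the primary (Fisher's exact test, odds ratio) does not fit the procedure-dependent outcomes or the admission count, and is exposed to unequal losses for haemorrhage and neurological events

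*Protocol article*

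**What the plan says.** In the Statistics section of the protocol article, the primary outcome of the first RCT "will be analyzed using a Fisher’s exact test and the odds ratio with 95" percent confidence interval. Two sentences later comes the rule at issue: "All other secondary objectives and analyses for this first RCT will be analyzed in the same way". No exception is given.

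The Outcomes section lists ten secondary outcomes, which are of different kinds:

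- Binary at fixed times: overall mortality, and mRS above 2 at 1, 5 and 10 years.
- Tied to a procedure: permanent disabling peri-operative complications; "the incidence of any peri-operative (within 31 days) complication"; peri-treatment stay over 15 days; and "occurrence of failure to eradicate the AVM (as determined by angiography) using the intended treatment modality".
- Partly a count: "the incidence and number of hospital admissions".
- Events over follow-up: any neurological event, and intracranial haemorrhage (ICH) up to 10 years.
- Unclear: discharge to a location other than home, which is listed beside the peri-treatment stay but is not itself tied to treatment.

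On the conservative arm, the Medical management section says: "Patients allocated to the medical management arm will receive no additional interventional treatment". The secondary hypotheses under Number of patients express the acceptable up-front risk of curative treatment as an absolute rate of permanent disabling complications (10 to 20% or less, by AVM grade), not as a contrast between arms.

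**The concern.** One test is prescribed for outcomes that need different analyses.

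For outcomes that need a procedure, a test between a treated arm and an untreated arm mainly shows that one arm was treated. It does not answer the article's own question, which is whether the procedural risk stays under a stated ceiling. A rate that the article accepts would be reported as an overwhelming difference.

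For the number of admissions, a two-by-two table discards the number.

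For ICH and neurological events, an ever/never proportion takes no account of how long each patient was observed. ICH is the event that intervention is meant to prevent, so a distorted comparison there would matter most among the secondary results.

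**Working it through.** **Reproducing the plan's own figure.** For 25% v 15%, two-sided 5% and 80% power (power and sidedness are not stated; these values reproduce the figure), n = [1.96·√(2·0.2·0.8) + 0.842·√(0.25·0.75 + 0.15·0.85)]² / 0.10² = 250 per group. The continuity correction gives (250/4)·[1 + √(1 + 4/(250·0.10))]² = 270 per group, as stated. So 270 per arm is used below.

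**1. Procedure-dependent outcomes.** With a events of 270 in the intervention arm and 0 of 270 in the conservative arm, the sample odds ratio is infinite for any a above 0, and Fisher's two-sided p = 2·C(270,a)/C(540,a).

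| Intervention-arm events | Rate | Fisher p |
|---|---|---|
| 5 | 1.9% | 0.061 |
| 6 | 2.2% | 0.030 |
| 14 | 5.2% | 0.0001 |
| 27 | 10.0% | 7.5e-9 |
| 54 | 20.0% | 5.8e-18 |

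Significance is reached from 6 events. The article's acceptable range starts far above that.

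Cross-overs soften the zero without rescuing the comparison. If 10% of the conservative arm crosses over and has the same 10% complication rate (270·0.10·0.10, about 3 events), the odds ratio is (27·267)/(243·3) = 9.9. With 20% crossing over (about 5 events) it is (27·265)/(243·5) = 5.9. The procedural risk is identical in both cases; the odds ratio moves with the number who crossed over.

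A one-arm estimate does answer the stated question. Exact 95% intervals, taking all 270 as treated for illustration: 27/270 = 10.0% (6.7 to 14.2%); 54/270 = 20.0% (15.4 to 25.3%).

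**2. Number of admissions.** The document gives no admission rates, so these are assumed scenarios: 270 per arm, gamma-Poisson counts with overdispersion 1, 1,500 simulated trials, Fisher on any/none against a Wald test of the log ratio of means.

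| Mean admissions | Fisher, any/none | Ratio of means |
|---|---|---|
| 1.0 v 1.0 (no effect) | 4% reject | 5% reject |
| 1.0 v 1.35 | 39% power | 74% power |
| 2.0 v 2.6 | 25% power | 72% power |

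Fisher's test remains valid for any/none. The loss is of information.

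**3. ICH and neurological events.** The input is 2.2% per year, the annualised haemorrhage risk without intervention that the Background gives from the earlier randomised trial. The same hazard h is set in both arms, so there is no true difference. Loss at rate l per year is an assumption, as is counting a lost patient without a recorded ICH as ICH-free. The expected raw proportion is h/(h+l)·[1 − exp(−10(h+l))]. Rejection rates come from 2,000 simulated trials.

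| Lost by 10 years (arm v arm) | Expected raw ICH | Fisher rejects |
|---|---|---|
| 0% v 0% | 19.7% v 19.7% | 4.4% |
| 18% v 18% | 18.0% v 18.0% | 4.4% |
| 18% v 39% | 18.0% v 15.7% | 8% |
| 18% v 55% | 18.0% v 13.8% | 22% |
| 10% v 63% | 18.8% v 12.7% | 44% |

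Equal loss leaves the test's size intact; unequal loss does not.

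Death is different. If 10% of an arm died at the outset and there were no losses, the raw 10-year ICH proportion would be 0.90·(1 − 0.978^10) = 0.90·19.95% = 17.95%. Cumulative incidence with death as a competing event gives the same 17.95%, because the dead stay in the denominator under both.

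**The case against.** The strongest reply is that this is one over-general sentence about secondary outcomes, and that the article already uses the procedural outcomes sensibly elsewhere. The secondary hypotheses give absolute thresholds, Trial monitoring has the safety committee compare treatment-related complications with confidence intervals, and the Discussion says the secondary endpoints were chosen so that the committee can watch immediate treatment results. That is fair and limits the weight of the point. It also shows that the sentence in Statistics conflicts with the article's own framing. Nor is this a matter left to an analysis plan, since the article states the rule outright.

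Three stronger readings are tempting, and the document does not support them.

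- A reader might infer that the procedural outcomes are exactly 0% or 100% in the conservative arm. Cross-overs stay in the study and the analysis includes intention-to-treat, so a few peri-operative events can occur there. A conservatively managed patient admitted with a haemorrhage could also be discharged elsewhere than home.
- A reader might count every conservative patient as a failure to eradicate and obtain an extreme p-value. The outcome concerns failure with the intended modality, and Table 1 records it only in the treatment column. For an untreated patient it is better read as not applicable.
- A reader might infer that the ICH comparison is biased as planned, or that early deaths bias it. Follow-up is a fixed 10 years, Fisher's test keeps its size with complete or equal follow-up, and death alone produces no departure from a competing-risk estimate. Only unequal loss does harm. The article expects losses but calls it too early to estimate them.

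**Conclusion.** The point holds as a defect in the wording of the secondary analyses.

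It is firm for the four procedure-dependent outcomes: apart from cross-overs, the prescribed test shows only that one arm was treated, and 27/270 v 0/270 gives p of about 7.5e-9 with an infinite odds ratio at a rate the article accepts. It is also firm for the number of admissions, which Fisher's test cannot analyse as a number. The size of the power loss there rests on assumed means and overdispersion.

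It is conditional for ICH and neurological events. Differential loss is plausible in an open 10-year trial in which the article itself expects that losses may be large, but nothing in the document quantifies it. The three-category and best/worst-case handling of losses is described for the primary analyses, and the article does not say that it extends to these outcomes.

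Mortality and mRS above 2 at fixed times are adequately served by the stated method. The primary analysis and sample size are unaffected.

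**What to change.** Replace the single sentence in Statistics with rules by type of outcome:

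- **Procedure-dependent outcomes** (both peri-operative complication outcomes, peri-treatment stay over 15 days, failure to eradicate): proportions with exact 95% confidence intervals in treated patients, by modality, with no between-arm test. Judge permanent disabling complications against the thresholds already given in the secondary hypotheses. State whether discharge other than home refers to the treatment admission; if so, it belongs here.
- **Number of admissions:** a rate ratio, for example negative binomial regression with follow-up time as offset.
- **ICH and neurological events:** cumulative incidence with censoring at loss to follow-up and death as a competing event, using event dates or, failing those, visit intervals.
- **Mortality and mRS above 2 at fixed times:** keep Fisher's exact test with the odds ratio.

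The cost is slightly more analysis work. The article does not say that event dates are collected; it describes asking about events at scheduled visits, so timing may be known only to the visit interval. Cumulative incidence censored at loss also assumes that loss is unrelated to the risk of the event, so it reduces the problem of unequal loss but does not remove it. Intervals by modality will be wider than those shown for 270 patients. The visit schedule, sample size and primary analysis stay as they are.

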## Discussion

One of the difficulties that has delayed the design of trials on AVMs is the relatively small number of heterogeneous patients treated by multiple treatment modalities, which renders well-powered randomized studies addressing specific questions on each treatment option difficult to conceive. To mitigate this difficulty, we have chosen to design a single trial and registry and keep inclusion criteria as broad as possible. The reason is that the most urgent necessity is to provide patients with a randomized trial context within which promising but unvalidated care can be provided in a large collaborative effort. This choice of study design has two correlates: the first is that as currently conceived TOBAS raises a general question as to whether unruptured AVMs should be treated. Although the number of patients for whom the uncertainty is present may be quite large, reasons are multiple and varied. For many clinicians these are as many, distinct research questions regarding what are considered heterogeneous groups of patients or lesions that should not be lumped together into an overall outcome result, for fear of averaging results that would have pulled in opposite directions. We must, however, remember the first goal of care trials: to protect present patients from unjustified beliefs and hypotheses, and offer optimal care in the presence of uncertainty [41]. From an organizational perspective, it is easier to propose a single inclusive large trial than to multiply small trials with narrow selection criteria. TOBAS could be split into five different trials or more. Given the difficulties with recruitment that were previously encountered in ARUBA, it is difficult to predict which ‘trial’ would recruit. It is possible, however, to pre-specify subgroups that will be individually monitored by the DSMC. Thus, the second implication of our design choice is that the DSMC must regularly be provided with subgroup-specific safety data to ensure that an emerging obvious discrepancy in clinical outcome will be addressed in a timely manner in order to prevent additional patient morbidity. We will then be in a position to identify which treatment modality and which patients should be submitted to randomized allocation as the trial progresses. Because each treatment modality should eventually be validated as beneficial before it becomes accepted as standard care, we may have to adjust hypotheses and the number of recruited patients as the trial proceeds, to eventually come up with answers that can apply in clinical practice.

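### First RCT: the three modality comparisons are set as separate Fisher tests at 5 % with no test of whether the effect differs by modality, so a uniform effect would usually look modality-specific

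*Protocol article*

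**What the plan says.** The method for the modality comparisons has to be put together from several places in the protocol article.

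- **Statistics, Table 2.** Under the stratified randomized allocation, the overall comparison is followed by three modality rows. The first is "Surgery subgroup versus Observation subgroup"; radiosurgery and embolization follow in the same form.
- **Statistics, test.** The primary outcome of the first RCT, in unruptured patients, "will be analyzed using a Fisher’s exact test and the odds ratio with 95 % confidence interval will be reported". Then: "All other secondary objectives and analyses for this first RCT will be analyzed in the same way".
- **Statistics, subgroups and level.** "Predetermined subgroups that will be examined include: 1) according to treatment modality", followed by presentation and Spetzler-Martin (SM) grade. The closing sentence runs every analysis "using a significance level of 5" per cent.
- **Number of patients.** About 540 patients (270 per group) are planned to detect a fall in poor outcome from 25 % to 15 %, with all modalities pooled. The same section says that validating each modality would in theory take 540 or more patients per modality.
- **Randomization.** The first randomization is stratified by intended modality (surgery, radiation therapy, embolization).
- **Discussion.** The authors hold that "each treatment modality should eventually be validated as beneficial before it becomes accepted as standard care".

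No interaction or heterogeneity test is named in the article.

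**The concern.** A Fisher test within one modality asks whether intervention differs from observation in patients intended for that modality. It does not ask whether the effect differs between modalities. When three such tests are run at 5 %, each on a fraction of the sample sized for the pooled question, some will often reach significance and others will not, even if the true effect is identical in all three.

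The Discussion expects to learn from subgroup data which modalities and patients should be submitted to randomized allocation. A chance mixture of significant and non-significant modalities could be taken as that answer: one modality judged beneficial and another not, with no evidence that they differ.

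**Working it through.** **Inputs.** From the article: 25 % versus 15 % poor outcome at 10 years, 270 per arm, 1:1 allocation, Fisher's exact test, 5 % level, three modality strata. Assumed: a two-sided test, the sizes of the strata (not stated), all 540 patients in the primary unruptured population, and no cross-over or loss to follow-up.

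**Step 1: reproduce the planned size.** With p1 = 0.25, p2 = 0.15, mean 0.20 and d = 0.10, at two-sided 5 % and 80 % power:

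n = [1.96·√(2·0.20·0.80) + 0.8416·√(0.25·0.75 + 0.15·0.85)]² / d² = (1.1087 + 0.4723)² / 0.01 ≈ 250 per arm.

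Continuity correction: n' = (n/4)·[1 + √(1 + 4/(n·d))]² = 62.5·(1 + √1.16)² ≈ 270 per arm, or 540 in all. This matches the plan exactly. The power is not stated in the article; 80 % is inferred from the match. Exact Fisher power at 270 per arm is 80.6 %.

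**Step 2: power within each modality under a uniform effect.** Exact Fisher power is the sum of the two binomial probabilities over all tables with p ≤ 0.05 in favour of intervention. The strata contain different patients, so their tests are independent. Hence P(all) = Π power, P(none) = Π(1 − power), and P(mixed) = 1 − P(all) − P(none).

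| Assumed patients per arm by modality | Power | All three significant | None | Some but not all |
|---|---|---|---|---|
| 90 / 90 / 90 | 32 % each | 3 % | 31 % | 66 % |
| 135 / 81 / 54 | 48 / 28 / 18 % | 2 % | 31 % | 67 % |
| 190 / 50 / 30 | 64 / 17 / 9 % | 1 % | 27 % | 72 % |

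For the first row: 0.323³ = 0.034; 0.677³ = 0.310; 1 − 0.034 − 0.310 = 0.656.

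In 20,000 simulated trials per split, the mixed share among trials with a significant overall result was 77 % to 85 %. The mixed pattern is therefore most common when the trial succeeds.

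**Step 3: the same data with a heterogeneity test.** A chi-square test on the three log odds ratios (2 degrees of freedom, 5 %) signals differing effects in about 3–4 % of these uniform-effect trials.

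**Step 4: what that test can detect.** Suppose two modalities have 25 % versus 15 % and the third has 25 % in both arms. Simulated power is about 22 % for 90/90/90, and about 11–12 % for 190/50/30 when the stratum without effect is the smallest. The test protects against false differences but would often miss real ones.

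**Step 5: sensitivity to size.** If each modality had 540 patients, all three would be significant in 0.806³ = 52 % of trials, none in under 1 %, and the mixed share would be about 47 %.

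**The case against.** **An interaction test belongs in a fuller document.** The article refers to a complete protocol held elsewhere, and silence on an interaction model alone would be no finding. But for the modality comparisons the article is not silent: it gives the pairs, the test and the level. Still, the method is assembled from three places. The sentence on predetermined subgroups says only that they will be examined, and it stands in a paragraph that opens with the registry. The modality case therefore rests on Table 2 and the test wording, not on that sentence.

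**The separate comparisons are legitimate.** This stands. Randomization is stratified by intended modality, so each is a valid randomized comparison and answers a question the plan asks. A reader might infer that the plan's method answers the wrong question; the documents do not support that. The fault is that nothing accompanies the three p-values to stop them being read against each other. The Discussion's caveat about comparing interventions concerns patients eligible for more than one option, and does not fill that gap.

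**The numbers may grow.** The Discussion foresees changing hypotheses and sample size, and with 540 per modality a mixed verdict would no longer be the usual one (Step 5). But about 540 in all is the number the plan fixes.

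**The same fault elsewhere.** A reader might extend the point to presentation, SM grade and the nested trial. The article does not support that firmly. The grade rows of Table 2 carry no comparison. For presentation the plan sets a hierarchy: unruptured patients are the primary population, and for ruptured patients "The same analysis will be performed for the ruptured group (considered a secondary analysis"). The nested trial uses an adjusted logistic model and only presents stratified results.

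**Conclusion.** The point holds for the three modality comparisons of the first RCT. They are fixed as separate Fisher tests at 5 %, on a total that the plan itself regards as enough for only one such question, with no test of whether the effect differs by modality. Under a uniform 25 % versus 15 % effect, the verdicts would be mixed in about 66–72 % of trials and all three significant in 1–3 %.

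This rests on assumed stratum sizes, though the mixed share exceeded 65 % in every split tried. It also rests on the p-values being read against each other, which the article does not prescribe but does nothing to prevent. Cross-overs and losses would lower power in each stratum further.

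A reader might also infer that the trial's main error rate is inflated. It is not: each RCT has its own named primary analysis, and these are secondary comparisons.

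**What to change.** State that the 5 % level applies to the primary comparison of each RCT. For the modality question, among unruptured patients, fit a logistic model for the primary outcome with allocated arm, intended modality (the randomization stratum) and their interaction. Report the interaction p-value and the three modality-specific odds ratios with 95 % confidence intervals. Label these as exploratory, with no claim of significance within a modality at the planned size.

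The same approach can be used for SM grade, and for intervention type in the nested trial, if those subgroups are to be tested. Ruptured patients stay in their separate secondary analysis.

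The cost is a short paragraph and one additional model; patients, data and sample size are unaffected. There are two downsides. No single modality can be declared effective on its own p-value. And because the interaction test is weak at this size, the text should say that a non-significant interaction is not evidence of equal effects.
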